#### Secondary outcome for children (based on parents’ assessments)

Effect from the program on the well-being in terms of social and emotional development of the child is expected at T3, T4, and T5.

The child’s social and emotional development is measured at T1, T2, T3, T4, and T5 with the *Ages & Stages Questionnaires – Socio-Emotional Second Edition* (ASQ:SE-2) [26]. It consists of 29–35 questions depending on the age, with 3-point scale response alternatives ranging from “often or always,” “sometimes,” to “seldom or never”. The parent can also indicate whether they worry about the behaviors. The ASQ:SE-2 ends with two open-ended questions.

To assess psychological and behavioral problems in the child, we use parents’ assessments of the *Strengths and Difficulties Questionnaire* (SDQ) [27] at the child age 3 years. The SDQ relates to the child’s behavior over the last 6 months and includes 25 questions that are answered on a 3-point scale with the alternatives “not true at all,” somewhat true,” and “completely true.” The SDQ is only measured at T5.

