### Outcomes {12}

Data are collected at five time points (Table 2): baseline (T1 – infant age 12–18 months), post-intervention (T2 – infant age about 14–20 months), after 6 months (T3 infant age 18–24 months), after 12 months (T4 – infant age 24–30 months), and in conjunction with the CHC visit when the child is 3 years old (T5). The data are collected through questionnaires to the parents. The baseline questionnaire contains background questions on the age and sex of the child and the parent and questions on parental educational level, country of birth, and family composition as well as several validated instruments that are repeated in the follow-up questionnaires.

**Table 2 Tab2:** Time points for the specific outcome measures and intervention assessments

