## Statistical methods

### Statistical methods for primary and secondary outcomes {20a}

The SPSS and R software will be used for all statistical analyses. Data will be tested for assumptions of parametric statistics. Examinations of pattern and amount of missing data will be performed and if appropriate treated by using relevant estimates. Statistical tests will be two-sided, and the level of significance will be set to 0.05.

Family and infant characteristics will at baseline be summarized overall and by trial arms, with means and standard deviations or medians and ranges for continuous variables. Numbers and percentages will be used for categorical variables. Summarized baseline measures regarding parental strategies and child well-being will also be shown. Any differences between groups at baseline will be examined with *t*-test for independent samples, chi-square test, or Mann–Whitney *U* test.

Fidelity measured as the group leader’s adherence to the program and parents’ participation in *Little ACF* or digital sessions will be summarized with descriptive statistics. Researchers performing statistical analyses of the primary outcome will be blinded to intervention allocation (*Little ACF* or digital session). Measures of effect size will be estimated to assess intervention effects. Hierarchical regression model will be used for assessing primary and secondary outcomes. Linear mixed regression model will be used for continuous data and generalized mixed models for binary and ordinal data. Intervention effects will be assessed for the primary outcome at the post-intervention and at the follow-ups with control for baseline scores. For the secondary outcome, intervention effects will be measured at the follow-ups with control for baseline and post-intervention scores.

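### Adjust the ASQ:SE-2 analyses for child age: the item set depends on age, yet the only covariates named are earlier scores (a small precision point, no bias)

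*Protocol article*

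**What the plan says.** The section on the secondary outcome for children names the ASQ:SE-2 and its schedule: "The child’s social and emotional development is measured at T1, T2, T3, T4, and T5". It then says of the instrument: "It consists of 29–35 questions depending on the age, with 3-point scale response alternatives".

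Outcomes {12} gives the child's age at each assessment: "baseline (T1 – infant age 12–18 months), post-intervention (T2 – infant age about 14–20 months"), then "after 6 months (T3 infant age 18–24 months), after 12 months (T4 – infant age 24–30 months"), and last "in conjunction with the CHC visit when the child is 3 years old (T5"). The same section lists the child's age among the background questions at baseline.

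Statistical methods {20a} sets the model class by type of data: "Linear mixed regression model will be used for continuous data and generalized mixed models for binary and ordinal data". For the secondary outcome it adjusts the follow-up comparisons for the scores at baseline and at T2. It names no term for child age or questionnaire form. It does not say how the ASQ:SE-2 is scored, nor which of the two model classes it falls under.

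**The concern.** By the protocol's own description the instrument changes with age. Two children at the same time point can be up to six months apart, so they may answer different numbers of questions. A child followed from T1 to T5 goes from 12–18 months to 3 years, so the form used at baseline may differ from the form used later.

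A raw sum over 35 items is not on the same scale as a raw sum over 29. If raw totals are modelled, part of the spread between children reflects only which form they were given. The earlier scores used as covariates carry the same mixture, so they predict the later score less well than they could. This also applies at T5, where the outcome age is nominally the same for all children but the baseline ages are not.

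What is at stake is precision on the only child outcome measured repeatedly. The validity of the comparison between arms is not at stake.

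**Working it through.** **Inputs from the protocol article**
- Item count 29 to 35, depending on age (secondary outcome for children).
- Age windows at T1 to T5 (Outcomes {12}).
- 251 per group, d = 0.25, power 80%, 25% drop-out, 670 in total (Sample size {14}). Two-sided 0.05 ({20a}).

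**Assumptions, not in the article**
- A raw total is analysed, and d = 0.25 applies to it. The article gives this d for parental self-efficacy only.
- Mean/SD of the raw total, m, lies between 0.5 and 3, with the mean taken at the 32-item midpoint.
- Half the children at a time point answer 29 items and half answer 35. This is the worst case for item count.
- Both forms have the same within-form SD and the same average item score.
- The comparison is a simple one of two arms, with nothing absorbed by earlier scores.

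**Step 1: reproduce the plan's figures.** n per arm = 2 × (1.960 + 0.842)² / 0.25² = 251.2, which agrees with 251. Power at 251 per arm is 79.97%. For drop-out, 502 / 0.75 = 669.3, so 670. Both figures reproduce.

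**Step 2: age spread at one time point.** T1: 18 − 12 = 6 months. T2: 20 − 14 = 6. T3: 24 − 18 = 6. T4: 30 − 24 = 6. T5 is one nominal age.

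**Step 3: shift due to item count.** With equal average item scores, the ratio of raw totals is 35/29 = 1.207. In SD units the difference between forms is Δ = (35 − 29)/32 × m = 0.1875 × m.

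**Step 4: effect on error variance and power.** Leaving out a form indicator with share p multiplies the error variance by V = 1 + p(1 − p)Δ², which is 1 + 0.25Δ² at p = 0.5. Power = Φ(0.25/√V × √(251/2) − 1.960).

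For m = 3: Δ = 0.5625; V = 1 + 0.25 × 0.3164 = 1.079; 0.25/√1.079 = 0.2407; 0.2407 × 11.203 = 2.697; Φ(2.697 − 1.960) = 76.9%.

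| Assumed mean/SD | Δ (SD) | Variance factor | Power at 251 per arm | n per arm for 80% |
|---|---|---|---|---|
| 0.5 | 0.09 | 1.002 | 79.9% | 252 |
| 1 | 0.19 | 1.009 | 79.6% | 254 |
| 1.5 | 0.28 | 1.020 | 79.2% | 257 |
| 2 | 0.38 | 1.035 | 78.6% | 260 |
| 3 | 0.56 | 1.079 | 76.9% | 272 |

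**Step 5: larger differences between forms.** If forms also differed in content or difficulty, Δ could exceed what item count gives. The same formula gives power of 74.6% at Δ = 0.75 and 70.7% at Δ = 1.0. Nothing in the article indicates differences of that size.

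**Step 6: validity.** 20,000 trials with 251 per arm were simulated with no treatment effect, two forms in equal shares, and form ignored in the test. The mean difference between arms was −0.0003 at Δ = 0.4 and −0.0001 at Δ = 1.0. The rejection rates were 5.0% and 5.1%.

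**The case against.** The strongest reply is that scoring and extra covariates for a secondary outcome are ordinary analysis-plan content, and that plan is not at hand. The article does not say that a raw total will be modelled as continuous: {20a} assigns the ASQ:SE-2 to no model class, and an item mean, a standardised score or a cut-off would all fit the text. Adjusting for earlier scores would also absorb part of any age or form difference, and randomisation balances age between arms in expectation.

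Most of this stands. It rules out calling the text an error, and it makes the loss conditional on raw totals being used. It does not remove the point about the covariates. The article does name the adjustment set for this outcome, and child age is not in it, although the item set depends on age and age is already recorded.

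A reader might infer more than the documents support:

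- **That several forms are in use at every time point.** The article gives no age limits for the forms, and T5 is one nominal age. Mixed forms at T1 to T4 are possible but not shown.
- **That baseline ages spread wider than six months, because recruitment starts at the 10-month visit.** Outcomes {12} puts T1 at 12–18 months; an earlier baseline is possible but not stated.
- **That mean trends from T1 to T5 would be spoiled.** No such trend analysis is planned; {20a} describes intervention effects adjusted for earlier scores.
- **That the SDQ model needs the same age term.** The SDQ has 25 questions, is given once, at age 3, and has no stated form problem.
- **That a set percentage reduction in standard error can be promised.** The article gives no share of variance explained by age or form.

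**Conclusion.** The point holds as a minor improvement. The ASQ:SE-2 item set depends on age, ages spread over six months at T1 to T4, and the named covariates are earlier scores only. If raw totals are analysed as continuous, the age and form differences that those scores leave over go into the residual.

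There is no bias between arms, and type I error stays near 5%. For item count alone, power falls from 80% to between 79.9% and 76.9%, a loss of about 0 to 3 points; at a mean/SD of 2 or less the loss is at most about 1.4 points. These figures rest on the borrowed d, the assumed mean/SD range, an even split between the shortest and longest forms, and a comparison without earlier scores, so they indicate order of magnitude only. No figure in the protocol changes.

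**What to change.** 1. Add child age, as collected at baseline, as a covariate in the ASQ:SE-2 models. For T2 to T4, age at assessment is close to baseline age plus a planned interval, so the baseline value should serve. At T5 it still helps, because the baseline scores come from children of different ages.
2. If a continuous score is used, put it on a common scale across age forms. The choices are the mean item score, or a z-score within form and time point with both arms pooled. The mean item score corrects for length but not for differences in content. The z-score also aligns level and spread, but needs enough children per form. Standardising at each time point is necessary, because a form first used at a later age has no baseline data.
3. Fix the choice before the researchers are unblinded, and show raw totals by form alongside.

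The cost is one covariate already in the data and one scoring rule. The small downside is that effects appear in less familiar units, which the raw totals by form offset. If the analysis plan already contains these rules, nothing further is needed.

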### Objectives {7}

The aim of the study is to increase the knowledge on the effects of *Little ACF* on parents and children.

Our specific research questions are how *Little ACF* can:Strengthen strategies of emotional regulation in parents,Promote parenting practices,Promote child socio-emotional well-being,Lead to the reduction of child behavior problems (externalizing/internalizing), andEngage and retain parents in groups?

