### Trial design {8}

The study includes a two-arm parallel superiority RCT to evaluate the efficacy of *Little ACF* in comparison with four digital lectures covering child development and parenthood. The allocation ratio applied was 1:1.

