***Child well-being (through assessments of parents)***						
Child’s social and emotional development	X		X	X	X	X
Psychological and behavioral problems						X

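### The covariate rule for the secondary outcome (baseline and post-intervention scores) cannot be applied to the SDQ, which is collected only at T5; the SDQ needs its own rule, without a T2 score

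*Protocol article*

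**What the plan says.** Four parts of the protocol article bear on this point.

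- **Secondary outcome for children.** This section covers two parent-rated instruments. ASQ:SE-2 is collected at all five time points. For the other, "The SDQ is only measured at T5", when the child is 3 years old.
- **Table 2.** The row "Psychological and behavioral problems" has a single mark, under T5. The SDQ is the only instrument assigned to that row.
- **Statistical methods {20a}.** A linear mixed model is planned for continuous data. For the primary outcome: "Intervention effects will be assessed for the primary outcome at the post-intervention and at the follow-ups with control for baseline scores". For the secondary outcome: "For the secondary outcome, intervention effects will be measured at the follow-ups with control for baseline and post-intervention scores". The second sentence names no instrument and makes no exception for the SDQ.
- **Objectives {7}.** One research question is how the programme can "Lead to the reduction of child behavior problems (externalizing/internalizing". Trial design {8} describes a "two-arm parallel superiority RCT to evaluate the efficacy of" the programme, and states "The allocation ratio applied was 1:1".

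**The concern.** The schedule and the analysis rule do not fit together for one of the two child instruments. The rule asks for two earlier scores, and the SDQ has neither. An analyst who follows the article must depart from it, and can do so in three ways: no covariate, the T1 ASQ:SE-2 score, or the T1 and T2 ASQ:SE-2 scores.

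The third way stays closest to the printed rule and is the harmful one. T2 is measured after the intervention. If the programme has already changed the child's socio-emotional score by then, conditioning on that score takes part of the effect out of the SDQ comparison. The SDQ carries the objective on behaviour problems, so the choice should not be left until the T5 data are in hand.

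**Working it through.** **1. The passages side by side**

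| Instrument | T1 | T2 | T3 | T4 | T5 | Can the {20a} rule use its own scores? |
|---|---|---|---|---|---|---|
| ASQ:SE-2 | yes | yes | yes | yes | yes | Yes |
| SDQ | no | no | no | no | yes | No |

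**2. The plan's own figure, used only for scale**

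Sample size {14} gives d = 0.25, 5% significance level, 80% power, 251 per group and 25% drop-out. {20a} makes the tests two-sided.

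- n per arm = 2 × (z0.975 + z0.80)² / d² = 2 × (1.960 + 0.842)² / 0.25² = 251.16. The stated 251 is reproduced within rounding.
- 502 / (1 - 0.25) = 669.3, rounded up to 670, as stated.

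These figures were set for parental self-efficacy. The article gives no effect size for the SDQ, so the 0.25 SD used below is an assumption.

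**3. What the T1 ASQ:SE-2 covariate would add**

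Let r be the correlation between T1 ASQ:SE-2 and T5 SDQ. The documents do not give it, so a range is shown. With 251 analysed per arm:

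- variance factor = 1 - r²
- equivalent sample-size factor = 1 / (1 - r²)
- detectable difference = (1.960 + 0.842) × √(1 - r²) × √(2/251)
- power = Φ(0.25 / (√(1 - r²) × √(2/251)) - 1.960)

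| r | Variance factor | Sample-size factor | Power at 0.25 SD | Detectable difference (SD) |
|---|---|---|---|---|
| 0 | 1.00 | 1.00 | 80.0% | 0.250 |
| 0.2 | 0.96 | 1.04 | 81.6% | 0.245 |
| 0.3 | 0.91 | 1.10 | 83.5% | 0.239 |
| 0.5 | 0.75 | 1.33 | 89.9% | 0.217 |

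**4. What a T2 covariate would do**

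The simulation used 4,000 runs with 251 per arm, independent standard normal T1 scores and independent standard normal errors e:

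- T2 = 0.6 × T1 - 0.25 × arm + 0.8 × e1
- T5 SDQ = -0.125 × arm + 0.5 × T2 + √0.75 × e2

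The true total effect is -0.125 + 0.5 × (-0.25) = -0.25, half of it through T2. The within-arm correlation of T1 with T5 is 0.5 × 0.6 = 0.3.

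| Covariates in the T5 comparison | Mean estimate | Power |
|---|---|---|
| None | -0.249 | 79.4% |
| T1 | -0.249 | 83.6% |
| T1 and T2 | -0.124 | 35.3% |

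The first two analyses recover the total effect. The third recovers only the part that bypasses T2. In this linear set-up, if a share m of the effect runs through T2, adjustment for T2 leaves (1 - m) × (-0.25): -0.25 at m = 0, -0.125 at m = 0.5 and 0 at m = 1.

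All these calculations treat participants as independent and ignore clustering by family and parent group.

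**The case against.** The strongest reply is that {20a} does not mention SDQ scores. It speaks of the secondary outcome in the singular and of follow-ups in the plural. The outcome section opens by expecting effects on social and emotional development at T3, T4 and T5, which points to ASQ:SE-2, and the rule fits that instrument. The SDQ would then fall under the general mixed-model sentence, with its covariates left to a fuller document.

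This is a fair reading, and it limits the point: the article does not state a model containing baseline SDQ. It does not remove the point. The SDQ stands under the same secondary-outcome heading, the rule is written for that class without exception, and nothing tells the reader that the SDQ is outside it.

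A second reply also stands. A randomised comparison at T5 needs no baseline value to be valid. The covariate improves precision only, and at r = 0.2 the improvement is slight.

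Two stronger readings are tempting, and the documents support neither.

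- A reader might infer that a reduction in behaviour problems cannot be shown without a starting SDQ value. The trial is a 1:1 randomised superiority comparison, so a lower T5 score in the intervention arm validly estimates a reduction relative to control. Only within-child change is unobservable, and the objective does not promise that.
- A reader might infer that T5 carries the heaviest attrition. The article gives one overall drop-out figure, 25%, and none by time point.

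**Conclusion.** The point holds as a mismatch between the measurement schedule and the stated covariate rule. As written, the secondary-outcome rule cannot be applied to the SDQ with its own scores, and the nearest substitute for the missing T2 score would adjust for a post-randomisation variable.

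The mismatch follows from the text alone. The sizes rest on assumptions. The loss from T2 adjustment depends on how much of the effect runs through T2, and halving it is an illustration. The gain from T1 ASQ:SE-2 depends on an unknown r: about 4% less variance at 0.2, 9% at 0.3 and 25% at 0.5. The power figures also assume a 0.25 SD effect on the SDQ.

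The mismatch does not make the SDQ comparison invalid. Apart from missing data, the unadjusted T5 contrast is sound. This is a modest correction to a secondary outcome, worth making because that outcome answers a named objective.

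**What to change.** Add a separate sentence for the SDQ to Statistical methods {20a}: the effect is the between-arm difference at T5, estimated from the planned mixed model with adjustment for the T1 ASQ:SE-2 score and for no T2 score. State there that the secondary-outcome rule with baseline and post-intervention scores does not apply to the SDQ.

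Report results for the behaviour-problem objective as a difference from the control arm in parent-rated problems at age 3, not as a change within children.

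The cost is a few sentences. T1 ASQ:SE-2 is already collected, so no new data, visit or design change is needed. The wording should be fixed before the T5 SDQ data are analysed.

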#### Implementation and other factors that could affect the outcomes

Parents’ attendance at the group meetings is registered by the group leaders. The follow-up questionnaires also contain questions to the parents in the intervention group about how they have used the content from the group meetings, whether they have tested the content at home, and if they found it useful. The parents in the control group are asked if they viewed the digital lectures and if they considered them meaningful.

The group leaders complete a checklist after each meeting including questions about if they had time for the different modules, how the home exercises worked, how committed the parents were during the meeting, and how much use they had of their group leading skills. The group leaders are also asked whether they perceived that they had sufficient knowledge about the content, any challenges that came up and their perspective on the material for the meetings in addition to how many parents and children were present.

### Participant timeline {13}

Figure 2 gives an overview to the participant timeline in the study.

**Fig. 2 Fig2:**
[figure not shown]
Flowchart of the study and the participant timeline

### Sample size {14}

#### Power calculation

A previous RCT of the program ACF for parents of children 3–12 years of age showed an effect size (Cohen’s *d*) of 0.30 for parental self-efficacy [16]. We expect a slightly smaller effect (*d* = 0.25) because this study compares *Little ACF* with lectures while the previous study had a waitlist control group. A total of 251 participants in each group are therefore needed with a significance level of 95% (*p*-value 0.05) and a power of 80%. A drop-out of 25% is expected resulting in the need to include 670 families in total. Each group consists of parents to 5–8 children so about 60–70 groups are needed. Each group leader is expected to lead at least three groups which means that about 25 group leader pairs are needed in total.

### Recruitment {15}

#### Group leaders

The recruitment of group leaders started with an information letter to all managers at potential health care facilities. Most recruitment took place at the CHCs. If a CHC-nurse was interested to participate, the nurse was required to contact a potential group leader partner from the municipality or another facility from the civic society, e.g., the Swedish church. The group leaders had to register for the training in pairs (this was a prerequisite from the project team). Potentially interested group leaders were invited to a digital workshop. The next step was a digital workshop to all those who had registered to the training where the information became more detailed. The workshop started with a presentation followed by the opportunity for the coming group leaders to ask questions.

The group leaders participated in three days of training sessions scheduled for every other week to allow for them to run groups in between. The training included theory and practical exercises and supervision is offered monthly during the trial. The group leaders are expected to lead in total at least three groups during the trial.

#### Parents

Parents are asked for participation by the CHC-nurse at the child’s ordinary 10-, 12-, or 18-month visit at CHC. The recruitment of parents started on August 1^st^, 2022, when the study had been approved by the Swedish Ethical Review Authority (Dnr 2022–02,603-01).

